### Premature termination of the study

2.6

The study will be terminated prematurely if serious events, like falls that lead to hospitalization, related to the Strolll AR intervention at home are reported for more than two participants. A liability insurance is in place in accordance with the legal requirements in the Netherlands, specifically article 7 of the Medical Research Involving Human Subjects Act (in Dutch: Wet Medisch-wetenschappelijk Onderzoek met Mensen, WMO). This insurance provides cover for damage to research participants through injury or death caused by the study. The insurance applies to the damage that becomes apparent during the study or within 4 years after the end of the study.

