#### Practice with Strolll AR intervention supervised in clinic (2 weeks)

2.2.5

To make the participant familiar with the Strolll AR platform technology and procedures and to allow the therapist to evaluate safety aspects, the Strolll AR intervention starts with 1 to 3 supervised in-clinic sessions of (cueing-assisted) personalized AR exercises.

In these supervised sessions in the clinic, the therapist will also test and validate procedures to select and tailor effective assistive AR cues from a library of different AR cues (see Supplementary material S2 for the types of cues used in this study). This is needed for two reasons: (1) to test the premise that a one-size-fits-all cue does not exist as there is heterogeneity in the effect of cues among participants, (2) to ensure that the Strolll AR gait-and-balance exercises can be effectively assisted with personalized cues for those who need it (e.g., people experiencing freezing of gait or people with small steps and shuffling gait (16–18)). The so-obtained best cues for supporting gait, as evaluated subjectively using both the participant’s experience and the therapist’s impression, will be used during the remainder of the Strolll AR intervention for those who are deemed to benefit from it. We will document if AR cues are added to Strolll AR gait-and-balance exercises, and when applicable, specify the type of AR cues as well as their personalized parameters (intercue distance, height, width, audiofeedback, etc.).

To deliver the Strolll AR intervention, participants in this study will by default be equipped with Magic Leap 2 AR glasses for its unmatched vertical AR field of view. Special insert lenses from a complementary lens kit (supports 8 prescriptions from −2.0 to +3.0) made available at each clinical site will be used to correct vision for people wearing spectacles. In case vision cannot be corrected with these insert lenses (e.g., due to a special prescription not part of the lens kit), either tailored insert lenses will be ordered for Magic Leap 2 or Microsoft HoloLens 2 with a slightly smaller vertical AR field of view will be used which can be worn over spectacles to deliver the intervention.

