Once the participant is deemed sufficiently capable of using the Strolll AR platform technology independently at home in a safe manner (after training in the clinic with the therapist for one to maximally three sessions of 1 hour in 2 weeks), the participant will take the AR glasses home together with a complementary SIM-card equipped WiFi router to continue the Strolll AR intervention independently at home. If the Strolll AR intervention at home is not deemed safe or suitable by the therapist, the intervention will stop and the reason for this will be documented by the therapist as part of the clinical feasibility evaluation.

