**Figure 4 fig4:**
[figure not shown]
Strolll AR gait-and-balance exercises: Smash! [without **(A)** and with **(B)** assistive AR cues], Mole Patrolll **(C)**, Hot Buttons **(D)**, Basketballl **(E)**, Puzzle Walk **(F)**, Wobbly Waiter **(G)**, and Cue Challenge **(H)**.

Participants will be invited by their therapist to use Strolll AR minimally 5 times a week for 30 active minutes per day, resulting in the recommended 150 minutes per week (1, 7, 8). They can perform the exercises anytime during the day, in one bout or in multiple chunks during the day, with complementary AR cueing when deemed beneficial. The precise exercises, exercise duration, difficulty level, and order will be prescribed by the therapist via the Strolll web portal (Figure 5). Therapists were by default recommended to prescribe all AR exercises, as each AR exercise targets different aspects (see Supplementary material S2). However, they were allowed to make adjustments, if necessary, to align with the participant’s abilities and needs, as well as for practical considerations. The prescribed exercises will be evaluated and adjusted on a weekly basis in telephone calls, e-consults or during an onsite therapy session using information of the participant in combination with the feedback from exercises that are reported in the Strolll web portal, such as adherence and game-play and functional performance metrics (cf. Supplementary material S2). Adherence will be defined as the percentage of performed over prescribed gait-and-balance exercises [i.e., both frequency and session-duration adherence; (15)]. The data on game-play level and performance will be used to evaluate whether the exercise program was both progressive (increase in level) and achievable (consistently high game-play performance scores) as intended. The weekly contact moments with the therapist will also be used to ask if participants experienced any adverse events (safety flags). Specifically, safety will be evaluated as the number of adverse events due to the Strolll AR intervention, such as falls, dizziness, eye strain, and headache. Potential technical issues will be documented by the researcher, who will be available to provide technical support during the study based on email or telephone contact with the participants.

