### Sample size calculation

2.4

A convenience sample of 100 participants will be included and measured from approximately 10 clinics in a time frame of 9 months. This sample size will give the therapists of the clinics enough experience with the Strolll AR platform and intervention to evaluate feasibility from a therapists’ perspective (e.g., usability, acceptability, safety). For our effectiveness outcomes, an a-priori required sample-size calculation in G*Power 3.1.9.7 showed that 58 participants (i.e., 29 per group) is sufficient for identifying statistically significant between-group differences (usual care vs. Strolll AR intervention). This is based on 80% power and a two-tailed alpha error of 5% and a minimal improvement of 2.57 s in TUG [i.e., the average of the smallest detectable TUG difference of Lim et al. (40) and Huang et al. (41)] and an effect size of 0.755 [Cohen’s *d* statistic; SD of 3.4 s; (41)]. Accounting for approximately 10 dropouts during the usual-care period, approximately 10 exclusions during the pre-intervention in-clinic phase (i.e., participants deemed unable to take the glasses home after one-to-three in-clinic training sessions) and approximately 10 dropouts during the intervention period at home [estimates based on Hardeman et al. (15)], recruiting a total of 100 participants should be sufficient for obtaining the minimal groups sizes required for identifying between-group differences. As dropout rates are taken into account, participants who are not completing the study will not be replaced. Plans to reduce dropouts are a voucher as a token of appreciation for their participation, updates about study progression via a newsletter send to participants and therapists every 2 months to keep them involved in the study and having weekly online or onsite check-ins with the participating therapists.

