### Discontinuation or modification of allocated intervention

2.5

Participants can leave the study at any time for any reason if they wish to do so without any consequences. The researcher can decide to withdraw a participant from the study for urgent medical reasons or when medication dosage is changed during the study. Participants that are withdrawn will not be replaced, because the sample-size calculation takes such dropouts into account. Reasons for drop out or withdrawal will be collected. Dropouts during the intervention period will be asked to complete the UEQ and Strolll AR evaluation questionnaire to reduce potential bias in the study’s participant experience results which could become manifest if only data from participants completing the intervention would be taken into account. For the other clinical tests and questionnaires, dropouts will lead to missing data.

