#### Feasibility (safety, adherence, performance, and user experience)

2.7.2

Clinical feasibility will be evaluated on several aspects. First, to determine if the Strolll AR intervention can be safely performed at home, descriptive outcomes will be reported for safety (i.e., number of dropouts during training at home including the reasons for withdrawal, adverse events including a paired-samples *t*-test comparison of the average weekly number of falls experienced during usual-care and intervention periods), providing insight into the potential risks of the Strolll AR intervention.

Second, to determine if the Strolll AR intervention was adherable over the course of the intervention, we will conduct a repeated-measures one-way ANOVA with the within-subject factor Time (three levels) on adherence scores derived from the first, second, and third part of the intervention at home (i.e., default intervention period is 6 weeks, so adherence is derived over roughly two-weeks intervals). The assumption of sphericity will be checked according to Girden (43). If Greenhouse–Geisser’s epsilon exceeds 0.75, the Huynh-Feldt correction will be applied; otherwise, the Greenhouse–Geisser correction will be used. Effect sizes will be quantified with *η*_p_^2^. Paired-samples *t*-tests will be used for post-hoc comparisons of a significant main effect of Time. In addition, one sample *t*-tests against 100% will be performed for adherence scores at each Time point to determine whether or not there were systematic deviations from the prescribed treatment.

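### The study termination rule counts only serious events at home, although Strolll AR use begins in the clinic

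*Protocol article*

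**What the plan says.** Section 2.6 (Premature termination of the study) gives one criterion for ending the whole study early: that "serious events, like falls that lead to hospitalization, related to the Strolll AR intervention at home are reported for more than two participants".

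Section 2.2.5 places first use of the device before the home phase. It says that, partly "to allow the therapist to evaluate safety aspects, the Strolll AR intervention starts with 1 to 3 supervised in-clinic sessions". A participant goes home with the glasses once judged capable, "after training in the clinic with the therapist for one to maximally three sessions of 1 hour in 2 weeks". Section 2.7.2 takes the same view of when the intervention begins: its user-experience analysis includes everyone who began Strolll AR in the clinic.

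Two other provisions deal with safety, both for single participants. Section 2.2.5 stops the intervention "If the Strolll AR intervention at home is not deemed safe or suitable by the therapist". Section 2.5 adds: "The researcher can decide to withdraw a participant from the study for urgent medical reasons".

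The wording on when the intervention starts is not uniform. Section 2.4 allows for "approximately 10 exclusions during the pre-intervention in-clinic phase", and the abstract and section 2.1 set two weeks of clinic familiarization apart from the six-week intervention at home.

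**The concern.** A study-level stopping rule should cover participants from first exposure to the device. Here first exposure is in the clinic, in sessions held partly to judge safety, yet the rule is limited to events at home. Read literally, three participants could each have a related fall with hospitalization during clinic sessions and the count under section 2.6 would still be zero. A related serious event under supervision bears on whether others should go on using the device, and the rule as written does not take it into account.

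The mixed terminology adds to the problem. Because section 2.4 calls the clinic phase pre-intervention, someone applying the rule has a textual reason to leave clinic events out.

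**Working it through.** The plan gives no operating figure for the termination rule beyond its threshold. Its one computed design figure, 58 participants for the TUG comparison, reproduces (two-sample t-test, d = 0.755, two-sided 5%, 80% power: 28.53, so 29 per group) but has no bearing here. The check is mainly textual.

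**What each provision does with a related serious event in a clinic session**

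| Provision | Scope | Adds to the study-level count? |
|---|---|---|
| 2.6, termination rule | events related to use at home | No |
| 2.2.5, stop if home use is judged unsafe or unsuitable | one participant | No |
| 2.5, withdrawal for urgent medical reasons | one participant | No |
| 2.2.6 and 2.7.2, adverse events | no limit by setting | Recorded and reported, but tied to no stopping criterion |

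**People, from the planning losses in section 2.4**

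- Clinic starters: 100 − 10 usual-care dropouts = 90.
- Home starters: 90 − 10 clinic exclusions = 80.
- Completers: 80 − 10 home dropouts = 70.
- Exposed in the clinic only: 10/90 = 11.1%. All their exposure is outside the rule. For the other 80, only the clinic part is.

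**Exposure time**

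- Clinic: 90 × 1 h = 90 h to 90 × 3 h = 270 h (section 2.2.5).
- Home: section 2.2.6 asks for use "minimally 5 times a week for 30 active minutes per day, resulting in the recommended 150 minutes per week", so 6 × 150 min = 15 h each. This gives 70 × 15 = 1050 h if dropouts count as zero, and 80 × 15 = 1200 h if they count in full.
- Share outside the rule: 90/(90 + 1200) = 7.0% to 270/(270 + 1050) = 20.5%.

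The upper end stacks three full sessions for everyone on no home use by any dropout. It also counts whole clinic hours, including cue selection, as device use. Lower home adherence raises the share. The home dose is a minimum, so more use lowers it.

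**Illustration with assumed event rates**

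The documents give no serious-event rate, so the rates here are assumptions. Let X ~ Bin(80, p_home) and Y ~ Bin(90, p_clinic), taken as independent. The current rule is met with probability P(X ≥ 3); the extended rule with P(X + Y ≥ 3), which would count twice a person with events in both phases.

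| p_home | Current rule | p_clinic 0.2% | p_clinic 0.5% | p_clinic 1% |
|---|---|---|---|---|
| 0.5% | 0.8% | 2.1% | 5.4% | 14.2% |
| 1% | 4.7% | 7.6% | 13.1% | 24.2% |
| 2% | 21.6% | 26.3% | 33.7% | 45.7% |

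If risk per hour were the same in both settings, three clinic hours against 15 home hours would put p_clinic at 3/15 of p_home. At p_home = 1% that is 0.2%, and the probability moves from 4.7% to 7.6%. Supervision could make the clinic rate lower, and unfamiliarity with the device could make it higher. The conclusion does not rest on this table.

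**The case against.** The home scope has a visible rationale. In the clinic a therapist supervises each session and can stop the intervention for that person. The rule covers the phase that lacks this control, and *at home* may simply be the protocol's name for the main intervention. The rule is not said to be exclusive, monitoring follows national guidelines as approved by an ethics committee, and the full protocol behind the article may hold further criteria. Nothing in the document shows that a supervised event should weigh the same as an unsupervised one. The exposure share measures time, not risk.

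Much of this stands and limits the size of the point. It does not change what the stated rule counts. The therapist's and researcher's powers act on one participant at a time. The article also states the criterion with an explicit scope, so this is not a detail merely left out of a condensed text.

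A reader might infer more than the documents support:

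- *That clinic events go unrecorded.* They do not support this. Section 2.2.6 defines safety by adverse events due to the intervention, without limit by setting.
- *That clinic stops for safety drop out of the report, because the withdrawal item in section 2.7.2 is the "number of dropouts during training at home including the reasons for withdrawal".* That item answers the section's stated question, which is safety at home. Reasons for clinic stops are documented as part of feasibility (2.2.5), reasons for withdrawal are collected in general (2.5), and the fraction cleared for home use is reported (2.7.2). Which heading they appear under is a reporting preference.
- *That the study could not be stopped after clinic events.* Section 2.6 does not forbid it; it only leaves them out of its count.

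**Conclusion.** The point holds for the termination rule alone. As written, a related serious event in a clinic session does not count toward the only study-level stopping criterion given, although the protocol itself places the start of the intervention in the clinic.

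The effect is modest. The uncovered sessions are supervised. About 10 of 90 planned starters have clinic exposure only, and about 7% to 20% of planned exposure time lies outside the rule. These figures rest on the planned losses in section 2.4, full clinic hours counted as use, and home use at the recommended dose. They describe exposure, not risk. Without a serious-event rate, no number of missed terminations can be claimed.

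**What to change.** In section 2.6, count serious events related to Strolll AR from the first in-clinic session onward, whether in the clinic or at home, and keep the threshold of more than two participants. Count each participant once across both settings.

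The cost is a few words. No new data collection is needed, since therapists attend the clinic sessions and adverse events are not limited by setting. The downside is that the rule could be met slightly sooner.

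Section 2.3 expects the last T2 assessment in February 2025. If follow-up has closed, the rule can no longer be changed to any effect. The report should then state that the rule covered home events only and say whether any related serious event occurred in the clinic phase.

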### Statistical analysis

2.7

Data analysis will be performed in JASP (42). Missing data will be excluded analysis-by-analysis.

#### Group characterization

2.7.1

Descriptive statistics of demographics (i.e., age, gender, disease duration, and LEDD) and questionnaires and clinical tests (i.e., MoCA, MDS-UPDRS, NFOGQ, PASE, and falls history) will be used to characterize the study sample (*n* = 100). To identify potential differences between control and intervention groups after the randomizations, independent-samples *t*-tests will be used after confirming normality with Shapiro–Wilk tests (otherwise Mann–Whitney *U*-tests will be used) for all parameters except gender, for which a Chi-square test will be used to identify between-groups differences.

#### Feasibility (safety, adherence, performance, and user experience)

2.7.2

Clinical feasibility will be evaluated on several aspects. First, to determine if the Strolll AR intervention can be safely performed at home, descriptive outcomes will be reported for safety (i.e., number of dropouts during training at home including the reasons for withdrawal, adverse events including a paired-samples *t*-test comparison of the average weekly number of falls experienced during usual-care and intervention periods), providing insight into the potential risks of the Strolll AR intervention.

Second, to determine if the Strolll AR intervention was adherable over the course of the intervention, we will conduct a repeated-measures one-way ANOVA with the within-subject factor Time (three levels) on adherence scores derived from the first, second, and third part of the intervention at home (i.e., default intervention period is 6 weeks, so adherence is derived over roughly two-weeks intervals). The assumption of sphericity will be checked according to Girden (43). If Greenhouse–Geisser’s epsilon exceeds 0.75, the Huynh-Feldt correction will be applied; otherwise, the Greenhouse–Geisser correction will be used. Effect sizes will be quantified with *η*_p_^2^. Paired-samples *t*-tests will be used for post-hoc comparisons of a significant main effect of Time. In addition, one sample *t*-tests against 100% will be performed for adherence scores at each Time point to determine whether or not there were systematic deviations from the prescribed treatment.

Third, the pre-cursor of Strolll AR, Reality DTx^®^, was found to be a progressive-but-achievable intervention in a research setting (15), where researchers balanced and tailored task demands and capacity (i.e., not too easy to prevent boredom and not too difficult to prevent demotivation) when remotely prescribing the exercises based on weekly telephone calls with the participants and their performance data from the Strolll web portal. To determine if Strolll AR, delivered in the clinical pathway, also results in a progressive-but-achievable intervention (i.e., increasing exercise levels over weeks while maintaining high-performance scores), levels and performance scores for each game were subjected to repeated-measures ANOVAs (or their non-parametric equivalent) with the factor Time (3 levels, first, middle, last part), using paired-samples *t*-tests (or their non-parametric equivalent) post-hoc analyses for significant effects of Time. We expect to find strong main effects of Time for exercise levels (with post-hoc effects showing an increase in exercise levels), but not or less so for performance scores.

Fourth, user experience will inform on acceptability among people with Parkinson’s disease and among therapists (i.e., top-3 barriers and facilitators questionnaire and an in-depth focus group) and usability (UEQ from both participants and therapists) of the Strolll AR intervention. To evaluate participant experience, all participants who started with the Strolll AR intervention in the clinic will be analyzed collectively (i.e., intention-to-treat protocol) to avoid a selection bias of the people who completed the intervention. The UEQ will not be analyzed statistically but will be reported as descriptive outcomes and interpreted against known benchmark scores (37). Also, other participants’ or therapists’ reported outcome measures from the questionnaires will be reported as descriptive outcomes. Finally, the fraction of participants deemed eligible for performing the intervention at home after having had the in-clinic Strolll AR sessions will inform about the usability of the intervention.

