#### Midterm assessment (T1): effectiveness

2.2.4

For the midterm assessment, the standard clinical tests of gait, balance, and falls-risk indicators (TUG, FTSTS, 10MWT, Mini-BESTest) (Table 1) will again be administered by the therapist. In addition, the participants are asked to fill out the FES-I and 6-week falls history (to assess falls during the usual-care period) questionnaires at home (Table 1).

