#### Final assessment (T2): effectiveness and clinical feasibility

2.2.7

To be able to evaluate the effectiveness of the Strolll AR intervention, the therapist will again administer standard clinical tests of gait, balance, and falls risk (TUG, FTSTS, 10MWT, Mini-BESTest). Participants will fill out the FES-I questionnaire together with the researcher during a telephone call (Table 1).

Clinical feasibility of the Strolll AR platform according to the participants will be assessed in terms of user experience [i.e., the User Experience Questionnaire (UEQ); (37)], technology acceptance and use [i.e., questionnaire based on the Unified Theory of Acceptance and Use of Technology model (UTAUT; (38))], top-3 barriers and facilitators of Strolll AR, and intervention-specific questions regarding Strolll AR, including cueing if used during the intervention (see Supplementary material S3). Participants will also report their falls history during the intervention period. The questionnaires of the final assessment are completed through a telephone call with the participant to ensure comprehensibility, which was first assessed in think-aloud sessions with a number of participants (39). In light of the potential future implementation in the clinical pathway, therapists will also be asked about their experience with Strolll AR through a purpose-made questionnaire (see Supplementary material S4), including the technology acceptance and use questionnaire, the top-3 barriers and facilitators (assessed before training their first participants and after training their last participant), and the UEQ (assessed after their last participant completed the study). Furthermore, a focus group with the therapist will be organized after the study for an in-depth evaluation of the top-3 barriers and facilitators.

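### The paired falls comparison and the barriers and acceptance results cover completers only, although the plan promises to analyse participant experience in everyone who started in the clinic

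*Protocol article*

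**What the plan says.** All references are to the protocol article.

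**Falls.** Falls in the usual-care period come from the T1 questionnaire set, which includes the "6-week falls history (to assess falls during the usual-care period) questionnaires at home" (section 2.2.4). Falls in the intervention period come from the final assessment: "Participants will also report their falls history during the intervention period" (section 2.2.7; Table 1 marks falls history at T1 and T2). Section 2.7.2 then applies a paired t-test "comparison of the average weekly number of falls experienced during usual-care and intervention periods".

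**People who stop.** Section 2.5 reads: "Dropouts during the intervention period will be asked to complete the UEQ and Strolll AR evaluation questionnaire". It continues: "For the other clinical tests and questionnaires, dropouts will lead to missing data". Section 2.7 adds: "Missing data will be excluded analysis-by-analysis".

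**Participant experience.** Section 2.7.2 assesses acceptability through the top-3 barriers and facilitators and usability through the UEQ. It says that "all participants who started with the Strolll AR intervention in the clinic will be analyzed collectively", and gives avoidance of completer selection as the reason.

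**Expected losses.** Section 2.4 expects about 10 dropouts in usual care, "approximately 10 exclusions during the pre-intervention in-clinic phase", and about 10 dropouts at home, out of 100 recruited.

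**The concern.** Feasibility, which includes safety and user experience, is a primary study parameter. The falls comparison is the only planned analysis that sets falls on Strolll AR against falls under usual care. A person who falls at home and stops for that reason gives no T2 falls report, and so drops out of that comparison. The loss may be related to the outcome being tested.

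For participant experience the plan contradicts itself. It recognises that analysing completers alone would be selective, and names all clinic starters as the set to be analysed. Yet it asks dropouts for only two instruments. The barriers and facilitators list, which is the stated measure of acceptability, is not one of them. Nor is the technology acceptance questionnaire. Someone following the plan exactly would report completer-only results on these two instruments under a rule that says otherwise.

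**Working it through.** **The plan's own figure.** The only computed figure is the 58 participants in section 2.4. It reproduces: with d = 0.755 and a two-sided 5% t-test, power is 0.792 at 28 per group and 0.807 at 29 per group, so 2 × 29 = 58. This point does not depend on it.

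**Step 1. Who is in which analysis (losses from section 2.4).**
- Start in the clinic: 100 − 10 = 90
- Start at home: 90 − 10 = 80
- Reach T2: 80 − 10 = 70

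**Step 2. Who is missing.**
- Paired falls test: a person needs both the T1 and the T2 report. Among home starters, (80 − 70)/80 = 12.5% are absent. Home starters are the right denominator because the stated question is safety at home, and those stopped in the clinic never trained there.
- Barriers and acceptance: the promised set is all clinic starters. (90 − 70)/90 = 22.2% are absent.

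**Step 3. Which instruments are sought, by group.**

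| Instrument | Completers (about 70) | Home dropouts (about 10) | Stopped in clinic (about 10) |
|---|---|---|---|
| UEQ, evaluation questionnaire | yes | yes | unclear |
| Intervention-period falls history | yes | no | no |
| Top-3 barriers and facilitators | yes | no | no |
| Technology acceptance | yes | no | no |

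The entry is unclear because section 2.5 addresses dropouts in the intervention period. Section 2.2.5 says the intervention starts with the supervised clinic sessions, whereas section 2.4 calls that phase pre-intervention. On the first reading these people are asked for the UEQ; on the second they are not.

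**Step 4. How much it could matter (assumed values).** The document gives no fall rates. Let completers fall at weekly rate f and home dropouts at k × f.

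With each person counted equally, as in the planned test, the all-home-starter mean divided by the completer mean is (70 + 10k)/80:
- k = 1: 1.00
- k = 2: 90/80 = 1.13
- k = 3: 100/80 = 1.25
- k = 5: 120/80 = 1.50

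Weighted by time instead, with 6 weeks per completer and an assumed 3 weeks per dropout, the ratio is (420 + 30k)/450:
- k = 1: 1.00
- k = 2: 480/450 = 1.07
- k = 3: 510/450 = 1.13
- k = 5: 570/450 = 1.27

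Both series concern the intervention period only. The planned contrast is within person, so its shift also depends on how often the same people fell during usual care.

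For acceptability, suppose 80% of completers are positive and a fraction q of the 20 non-completers are. The all-starter figure is (70 × 0.80 + 20q)/90:
- q = 0: 56/90 = 62%
- q = 0.25: 61/90 = 68%
- q = 0.50: 66/90 = 73%

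**The case against.** The strongest reply is that people who stop are not lost from the safety evidence.

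- Section 2.2.6 has therapists ask about adverse events every week and names falls as an example.
- Reasons for withdrawal are collected (section 2.5) and reported with the home dropouts (section 2.7.2).
- Section 2.6 has a separate termination rule for serious events such as falls leading to hospitalization.
- For people stopped in the clinic, the therapist records why (section 2.2.5), and the fraction judged eligible for home use is reported (section 2.7.2).
- Home dropouts are asked for the UEQ and the evaluation questionnaire precisely to limit selection. The content of the evaluation questionnaire is in a supplement that is not shown.

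Much of this stands, and it rules out several stronger readings that a reader might infer:

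- *Dropouts are never asked about falls.* Not supported, because the weekly contacts may record them.
- *The all-starters set cannot be formed at all.* Not supported. For the UEQ and evaluation questionnaire it can be formed for home dropouts and, on the section 2.2.5 reading, for everyone.
- *A non-significant t-test will be taken as proof of safety.* Not stated. Section 2.7.2 presents safety descriptively, with the falls test as one component.
- *Unequal time at risk already distorts the planned test.* Largely not, because the outcome is a weekly average and completers have a default period of 6 weeks. Exposure matters once dropouts are added.

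The reply does not repair the falls comparison. Section 2.2.6 counts events due to the intervention. It describes no matching count for usual care and does not say that these events enter the paired test. Nor does the reply address the missing barriers and acceptance questionnaires.

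**Conclusion.** The concern holds in a limited form. As written, the paired falls comparison covers completers only, leaving out about 10 of 80 home starters (12.5%). The barriers and acceptance results omit about 20 of 90 clinic starters (22%), contrary to the all-starters rule in section 2.7.2. Whether the roughly 10 people stopped in the clinic are asked even for the UEQ is unclear, because sections 2.2.5 and 2.4 describe that phase differently.

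These fractions rest on the attrition expected in section 2.4. A reader might also conclude that the results must be biased in favour of the device. The document does not support that: it gives no fall or acceptance rates, and does not say that people who stop are those who fell or disliked the device. Under assumed dropout fall rates of 1 to 5 times the completers' rate, the all-home-starter mean would be 1.00 to 1.50 times the completer mean. At equal rates there is no bias.

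**What to change.** 1. Amend section 2.5 so that everyone who started in the clinic, including those stopped before going home, is asked the following when they stop: UEQ, Strolll AR evaluation, falls history, top-3 barriers and facilitators, and technology acceptance.
2. In section 2.7.2, compare falls in all home starters per week observed, for example as a within-person rate ratio of the intervention period to usual care with a 95% confidence interval. Report it alongside the descriptive adverse events. The choice of count model can be left to the analysis plan.
3. Reconcile sections 2.2.5, 2.4, 2.5 and 2.7.2 on whether the in-clinic phase belongs to the intervention period and who forms the participant-experience set.
4. Where these data cannot be obtained, label the falls, barriers and acceptance results as completer-only.

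**Cost.** A longer exit contact for about 10 home dropouts, a new short contact for about 10 people stopped in the clinic, and one changed analysis. Some people will decline, so the gap would shrink but probably not close.
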